### Ethics

This protocol (version. 1.0) was approved by the Ministry of Food and Drug Safety (date: March 16, 2022; Medical Device Approval # 1322). It was approved by the IRB of Kyung Hee University Korean Medicine Hospital (date: April 22, 2022; approval No.: KOMCIRB 2022-03-004-001) and Dongshin University Gwangju Korean Medicine Hospital (date: March 22, 2022; approval No.: DSGOH-2022-002). Participants and their companions will be informed of the study purpose and risks. All participants will provide written informed consent prior to participation.

### Randomization and allocation

The investigator will carry out a screening interview, and then the assessor will conduct baseline assessment. The 106 enrolled participants will be randomly allocated evenly to the 650 ILA or control group (*n* = 53 per group). The serial numbers will be generated by stratified block randomization using SAS^®^ version 9.4 (SAS Institute Inc., Cary, NC, USA). The serial numbers will be packed in opaque envelopes and stored in a cabinet with two locks.

The investigator managing the serial numbers will open the envelopes and assign participants to the investigator who will conduct the intervention.

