### Recruitment

We will recruit participants at the Kyung Hee University Korean Medicine Hospital and Dongshin University Gwangju Korean Medicine Hospital in the Republic of Korea *via* the use of posters, local newspapers, and the internet in hospitals and communities. Interested people will receive an explanation of this study from the clinical research coordinator (CRC) upon visiting the hospital and will provide written informed consent prior to participation.

At each visit, the CRC will explain the following visit schedule and will adjust the visit schedules for each participant to facilitate participation.

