### Outcome measurements

The primary outcome will be the between-group differences of the proportions of responders at 3 days after the intervention ends. A responder is defined as a participant who responds with more than 30% decrease in baseline VAS score without an increase in baseline use of painkillers (27, 28).

The secondary outcomes will include the between-group differences of changes in VAS, EQ-5D-5L, and ODI at 3 days after the treatment ends and 8 weeks after the treatment ends.

The VAS is a self-reported scale, usually a 100-mm-long straight line marked 0 for no pain and 100 for pain as intense as it could be (29). It is widely used to assess pain severity in LBP trials (30).

The EQ-5D is a generic assessment tool for measuring health-related quality of life (31). The EQ-5D-5L is a new version of the EQ-5D that extends the level of each dimension from three to five (32).

The ODI includes nine questions about interference with several physical activities and one question about pain intensity (33). We used the Korean version of the ODI, which excluded sexual life from the original ODI and has been validated (34).

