### Statistical analysis

The final data will be analyzed by a biostatistician not involved in the execution of our trial. The primary analysis population for assessing the efficacy of the intervention will be a full analysis set (FAS), while the supplementary analysis population will be a PPS. The results of the FAS and PPS analyses will be compared and reflected in the efficacy evaluation. “Multiple Imputation” method will be used to obtain the missing value. All analyses will be performed at the 5% (two-sided) significance level using SAS^®^ version 9.4 (SAS institute. Inc., Cary, NC, USA) software. We will not perform interim analyses.

Baseline characteristics and variables will be compared between the two groups. Categorical data will be compared using the Fisher’s exact test or chi-square test, while continuous data will be compared using the Wilcoxon’s rank sum test or independent *t*-test.

The difference in responder proportions will be tested using the chi-square test or Fisher’s exact test. The degrees of changes in the VAS, EQ-5D-5L, and ODI scores at 3 days after the treatment ends and 8 weeks after the intervention ends, relative to the baseline score, between the groups will be evaluated using analysis of covariance with baseline scores as covariates. Within each group, changes in VAS, EQ-5D-5L, and ODI scores at each time will be analyzed using one-way analysis of variance and a paired *t*-test or Wilcoxon signed rank test. Sub-analyses will be performed according to each institution.

A safety assessment will be conducted for all SAEs and AEs that will occur during the trial period. The incidences of SAEs and AEs will be compared between the two groups using chi-square test or Fisher’s exact test. A comparative analysis will be carried out between the groups for participants who will be out of normal range for a clinical laboratory test.

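### Randomisation is stratified, but the stated primary test and ANCOVA leave the stratum out; if it predicts response, the primary test is conservative and loses a few points of power

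*Protocol article*

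**What the plan says.** On allocation, the Randomization and allocation section states: "The serial numbers will be generated by stratified block randomization". No stratification factor is given. The Recruitment section names two centres: "We will recruit participants at the Kyung Hee University Korean Medicine Hospital and Dongshin University Gwangju Korean Medicine Hospital".

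On analysis, the Statistical analysis section fixes three things:
- Primary outcome: "The difference in responder proportions will be tested using the chi-square test or Fisher’s exact test". No stratum or covariate is attached.
- Changes in VAS, EQ-5D-5L and ODI: differences "between the groups will be evaluated using analysis of covariance with baseline scores as covariates". No stratum or site term is named.
- Institution: "Sub-analyses will be performed according to each institution". This is its only appearance in the analysis.

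Baseline VAS enters the primary outcome only through the responder definition in Outcome measurements, which requires "more than 30% decrease in baseline VAS score without an increase in baseline use of painkillers".

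**The concern.** Stratified blocking makes the arms alike within each stratum. If response differs between strata, part of the outcome variation can no longer contribute to chance differences between arms. A pooled two-by-two test still counts that variation in its standard error, so the standard error is too large and the test rejects too seldom. The same applies to an ANCOVA that omits the factor.

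A difference in response between the two hospitals is plausible. The practitioners know the allocation (Blinding section) and the outcome is self-reported pain. What is at stake is precision already obtained through the randomisation.

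A second, smaller matter is the by-institution sub-analyses. Each has little power, and the article states no site-adjusted estimate or interaction against which to read a disagreement between the hospitals.

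**Working it through.** **Inputs from the article.** Responder rates 30% (control) and 60% (650 ILA); two-sided alpha 0.05; power 0.80; 42 per arm evaluable; 53 per arm enrolled; 1:1 allocation; two hospitals. **Assumptions, because the article gives no figure:** the stratum is institution, the sites are of near-equal size, and site response rates vary over the range shown.

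**Step 1: the plan's own sample size.** n = (1.96·√(2·0.45·0.55) + 0.842·√(0.30·0.70 + 0.60·0.40))² / 0.30² = 41.98, so 42 per arm. Then 42/0.8 = 52.5, so 53 per arm and 106 in all. Both stated figures reproduce.

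**Step 2: why the unstratified test becomes conservative.** Under the null, take both arms at control rates of 10% and 50% at two equal sites. The overall rate is 30%.
- Variance per participant assumed by the pooled test: 0.30·0.70 = 0.21.
- Variance left after stratified allocation: (0.10·0.90 + 0.50·0.50)/2 = 0.17.
- Effective critical value: 1.96·√(0.21/0.17) = 2.18, a true size of about 2.9%.

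For 20% and 40%, the within-site variance is (0.16 + 0.24)/2 = 0.20. The critical value is 1.96·√(0.21/0.20) = 2.01, a size of about 4.5%.

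**Step 3: simulation at 53 per arm.** Unstratified chi-square (no continuity correction) against CMH, two near-equal sites balanced by arm. Power is for a 30-point effect at each site. Type I error has both arms at the control rates shown.

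| Control rates at the two sites | Type I error, crude / CMH | Power, crude / CMH |
|---|---|---|
| 30% / 30% | 5.3 / 5.0% | 87.8 / 87.7% |
| 20% / 40% | 4.7 / 5.0% | 88.4 / 90.2% |
| 10% / 50% | 3.1 / 4.9% | 90.2 / 93.9% |

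Repeat simulations differ from these figures by up to about 0.4 points. The sizes agree with step 2.

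**Step 4: the same power comparison at 42 per arm.**

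| Control rates at the two sites | Power, crude / CMH |
|---|---|
| 30% / 30% | 82.8 / 79.8% |
| 25% / 35% | 82.9 / 80.7% |
| 20% / 40% | 83.3 / 82.6% |
| 10% / 50% | 85.1 / 87.6% |

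At this size the crude test is ahead by 0.7 to 3.0 points until the sites differ widely.

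**Step 5: by-institution power from the plan's formula.** Power = Φ[(0.30·√n − 1.96·√0.495)/√0.45].
- n = 42: 80.0%, matching the plan.
- n = 21 per arm per site (evaluable, even split): (1.375 − 1.379)/0.671 = −0.006, so 50%.
- n = 26.5 (all enrolled, even split): (1.544 − 1.379)/0.671 = 0.246, so 60%.
- Fisher's exact test: 36% at 21 and 48% at 26 per arm.
- A 70:30 split of 53 per arm (37 and 16): 75% and 39%.

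Suppose the planned effect is equally real at both hospitals. The chance that one is significant and the other not is 2·0.50·0.50 = 50% at 50% power, or 2·0.60·0.40 = 48% at 60% power.

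**Step 6: baseline VAS.** This used a logistic likelihood-ratio test with site and baseline at 42 per arm, 3,000 runs per scenario. If baseline is strongly prognostic (log-odds 1.0 per SD), power rises from about 83% to 87–89%. If it is weak (0.5 per SD), the change is between −0.3 and +2 points.

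**The case against.** The strongest reply is that little is at risk. The unstratified test is unbiased, and leaving out a prognostic stratum makes it conservative rather than liberal. The planned 80% power is met by the chi-square in every scenario above. At 42 per arm with similar sites, CMH has slightly less power. All of this stands, and it keeps the point modest.

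It can also be said that the stratum is unnamed and that an unseen analysis plan may supply it. The first part stands: institution is an inference. The second carries less weight, because the article names the tests and the ANCOVA covariates and does not leave them open.

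A reader might infer more than the article supports:
- **That ignoring strata inflates the false-positive rate.** A crude size of 6.2% does occur at 42 per arm with no site difference and a 45% response in both arms. It comes from the discreteness of the uncorrected chi-square: at 53 per arm and the same null it is 4.7%. It is not an effect of omitting strata.
- **That the by-institution analyses replace adjustment.** The article lists them as additional. Low power is normal in a check of consistency between sites.
- **That omitting baseline VAS from the primary test is an error.** The responder definition is already relative to baseline, entry is restricted to VAS 35–74, and nothing in the article shows that baseline predicts percentage response.

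**Conclusion.** The point holds as a mismatch between the stated design and the stated analysis. It does not threaten validity or the sample size. If the stratum predicts response, the primary test runs below its nominal 5% (about 4.7% to 3.1% over the range examined). It then loses about 2 to 4 points of power against a stratified test at 53 per arm. If the stratum does not predict response, nothing is lost at that size.

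These figures rest on institution being the stratum, on an even site split, and on assumed site differences. The by-institution sub-analyses have about 50–60% power each under an even split and cannot carry a conclusion separately.

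**What to change.** Before unblinding:
1. Name the stratification factor.
2. Make the primary analysis a CMH test stratified by that factor, or a logistic regression including it, reported as a standardised risk difference with 95% CI.
3. Add the factor to each ANCOVA.
4. Label the by-institution results descriptive and give a treatment-by-institution interaction estimate beside them.
5. Treat baseline VAS in the primary model as an optional covariate of uncertain gain, to be decided in advance.

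Cost: wording only. Institution and baseline VAS are already recorded, and neither the sample size nor trial conduct changes. The one statistical cost is at 42 analysed per arm with no or small site differences. There CMH has about 1 to 3 points less power than the uncorrected chi-square (79.8% against 82.8% with none), because discreteness makes the chi-square slightly liberal at that size. At 53 per arm there is essentially no loss.

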### Implementation

The investigator managing the serial numbers will generate the randomization sequence and distribute participants to the groups. The CRC will enroll the participants.

### Blinding

The practitioner will insert the acupuncture needles into GB30, BL23, BL24, and BL25 and then operate the laser emitting device according to the treatment method of each group (650 ILA group, 20 mW power for 10 min; control group, 0 mW power for 10 min). Therefore, the practitioner who will conduct the intervention would know the group assignment of participant. Owing to the practitioner unblinding, we will adopt an assessor and patient-blinded design using sham ILA. During the course of the study, all investigators except those who will perform the intervention and manage the serial number codes will be blinded. However, if necessary, such as in the event of SAE, unblinding will be permitted under the IRB approval. This study will only include individuals without predetermined positions or competing interests.

### Interventions

Trained Korean medical doctors will administer the treatment. The investigators who will carry out the interventions will undergo joint training to ensure adherence to our protocol. ILA treatment will be conducted using a laser emitting device (Ellise; Wontech Co. Ltd., Daejeon, Republic of Korea) comprising an optical fiber-coupled laser diode (InGaAIP), a sterile acupuncture needle with optical fibers inserted therein, and a laser output device (Figure 1).

**FIGURE 1 F1:**
[figure not shown]
Invasive laser acupuncture (ILA) therapy.

The acupuncture needles will be vertically inserted into GB30, BL23, BL24, and BL25 and then the laser (650 ILA group, 20 mW power for 10 min; control group, 0 mW power for 10 min) will be turned on. The ILA parameters will be 50 Hz frequency, 20 mW power, 63.69 W/cm^2^ power density, 12 J/point energy dose, 38216.56 J/cm^2^ energy density, and pulse type wave. Participants will receive treatment for 10 min per visit, twice a week for 4 weeks. Based on previous RCTs investigating the efficacy of LLLT for NSCLBP (25, 26), the control group will receive the same procedure as the 650 ILA group. No significant differences in sound, feeling, or observation will be expected between the two groups. Hence, all participants will be blinded. The ILA treatment methods have been described in more details in our previous pilot study (20).

All participants will receive education on exercise and self-management during the treatment period (Visit 1–Visit 8). We will provide all participants with acetaminophen (500 mg), which can be taken when the pain is severe as a rescue regimen.

At each visit, the medical condition of the participants will be monitored to ensure that they adhere to the trial procedure. All participants will be expected to comply with the intervention protocol. However, the assessment and treatment schedule may be changed upon the request of the participant or in accordance with the judgment of the PI.

During the study period, all participants will not be permitted to receive other treatments (complementary and alternative therapies, physical therapy, or pharmacological treatments not allowed in our trial) for improving NSCLBP symptoms. However, they will be allowed to use pharmacological and non-pharmacological treatments for improving other symptoms.

### Outcome measurements

The primary outcome will be the between-group differences of the proportions of responders at 3 days after the intervention ends. A responder is defined as a participant who responds with more than 30% decrease in baseline VAS score without an increase in baseline use of painkillers (27, 28).

The secondary outcomes will include the between-group differences of changes in VAS, EQ-5D-5L, and ODI at 3 days after the treatment ends and 8 weeks after the treatment ends.

The VAS is a self-reported scale, usually a 100-mm-long straight line marked 0 for no pain and 100 for pain as intense as it could be (29). It is widely used to assess pain severity in LBP trials (30).

The EQ-5D is a generic assessment tool for measuring health-related quality of life (31). The EQ-5D-5L is a new version of the EQ-5D that extends the level of each dimension from three to five (32).

The ODI includes nine questions about interference with several physical activities and one question about pain intensity (33). We used the Korean version of the ODI, which excluded sexual life from the original ODI and has been validated (34).

### Adverse events

Adverse events (AEs) are unintentional and undesirable symptoms, signs, or diseases that appear during or after treatment in a clinical trial. In our pilot study, no AEs and SAEs were associated with laser irradiation (21). AEs that could occur in our trial include bleeding, pallor, local hematoma, skin irritation, objective worsening of pain, and dizziness or fainting. All the AEs and SAEs would be recorded in detail, including the potential causalities between the intervention and AE, degree of severity, time of occurrence, and any measures taken to improve AE by the CRC. They will be reported to the IRB. The occurrence rate of SAEs and AEs will be compared between the two groups in the safety assessment. Participants who will experience AEs and SAEs related to our intervention will be compensated according to the relevant regulations.

### Quality control

Our protocol has been developed and revised severally by experts in LA, NSCLBP, and statistics. Before the study, all investigators will be trained severally to fully understand the standard operating procedures (SOPs) of this trial and the protocol. An independent clinical research associate will monitor our study and check all the trial documents. Any revision of this protocol will be reviewed and approved by the Ministry of Food and Drug Safety and the IRB of Kyung Hee University Korean Medicine Hospital and Dongshin University Gwangju Korean Medicine Hospital.

### Sample size estimation

In our previous pilot study (21), the difference in proportion of responders between 650 ILA (93% [14/15]) and control groups (40% [6/15]) was 53%. To obtain sufficient clinical data, we determined the sample size assuming an expected responder proportion of 30% in the control group and 60% in the 650 ILA group, a two-sided alpha level of 0.05, and a statistical power of 0.8. Under these assumptions, a total of 84 (42 per group) participants will be required. Estimating a maximum dropout rate of 20%, 106 participants (53 in each group) will be required in our trial.

$$\frac{n={\left(z_{\alpha /2}\,\sqrt{2\,\bar{p}\,\bar{q}}+z_{\beta }\,\sqrt{p_{1}\,q_{1}+p_{2}\,q_{2}}\right)}^{2}}{{\left(p_{t}-p_{c}\right)}^{2}}=\frac{{\left(1.96\,\sqrt{2\times 0.45\times 0.55}+0.842\,\sqrt{0.30\times 0.70+0.60\times 0.40}\right)}^{2}}{{\left(0.60-0.30\right)}^{2}}\approx 42$$

### Statistical analysis

The final data will be analyzed by a biostatistician not involved in the execution of our trial. The primary analysis population for assessing the efficacy of the intervention will be a full analysis set (FAS), while the supplementary analysis population will be a PPS. The results of the FAS and PPS analyses will be compared and reflected in the efficacy evaluation. “Multiple Imputation” method will be used to obtain the missing value. All analyses will be performed at the 5% (two-sided) significance level using SAS^®^ version 9.4 (SAS institute. Inc., Cary, NC, USA) software. We will not perform interim analyses.

Baseline characteristics and variables will be compared between the two groups. Categorical data will be compared using the Fisher’s exact test or chi-square test, while continuous data will be compared using the Wilcoxon’s rank sum test or independent *t*-test.

The difference in responder proportions will be tested using the chi-square test or Fisher’s exact test. The degrees of changes in the VAS, EQ-5D-5L, and ODI scores at 3 days after the treatment ends and 8 weeks after the intervention ends, relative to the baseline score, between the groups will be evaluated using analysis of covariance with baseline scores as covariates. Within each group, changes in VAS, EQ-5D-5L, and ODI scores at each time will be analyzed using one-way analysis of variance and a paired *t*-test or Wilcoxon signed rank test. Sub-analyses will be performed according to each institution.

A safety assessment will be conducted for all SAEs and AEs that will occur during the trial period. The incidences of SAEs and AEs will be compared between the two groups using chi-square test or Fisher’s exact test. A comparative analysis will be carried out between the groups for participants who will be out of normal range for a clinical laboratory test.

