## Materials and analysis

### Aims

1)We will investigate the clinically persistent pain-reduction effect of 650 nm ILA for NSCLBP at 3 days after the end of intervention.2)We will investigate the pain reduction, functional limitation improvement, and quality of life improvement effects of 650 nm ILA for NSCLBP.3)We will investigate the safety of 650 nm ILA in patients with NSCLBP.

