### Hypothesis

1)The 650 ILA group will have a significantly higher proportion of responders than the control group at 3 days after the end of intervention.2)The 650 nm ILA will show improvements in pain intensity, quality of life, and functional limitation in patients with NSCLBP.3)The 650 nm ILA would be a safe treatment for patients with NSCLBP.

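### The within-group one-way ANOVA ignores that the same participants are measured repeatedly; it is too conservative and can contradict the paired tests planned beside it

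*Protocol article*

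**What the plan says.** In the protocol article, the Statistical analysis section gives two kinds of analysis for the three continuous scores.

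- **Between groups:** changes from baseline "between the groups will be evaluated using analysis of covariance with baseline scores as covariates".
- **Within each arm:** "Within each group, changes in VAS, EQ-5D-5L, and ODI scores at each time will be analyzed using one-way analysis of variance", followed in the same sentence by a paired t-test "or Wilcoxon signed rank test".

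The section does not say that the ANOVA is a repeated-measures one. It does not say which within-group result counts if the tests differ.

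The Outcome measurements section defines the secondary endpoints as comparisons: "The secondary outcomes will include the between-group differences of changes in VAS, EQ-5D-5L, and ODI". They are assessed twice after treatment, first at 3 days and again at 8 weeks. Table 1 places the VAS, EQ-5D-5L and ODI assessments in the Visit 1–2 column, at Visit 9 and at Visit 10.

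The first hypothesis is comparative: "The 650 ILA group will have a significantly higher proportion of responders than the control group". The second names no comparator: "The 650 nm ILA will show improvements in pain intensity, quality of life, and functional limitation in patients with NSCLBP".

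**The concern.** Inside one arm the only natural factor for a one-way ANOVA is time, and every level of that factor holds the same people. The ordinary one-way ANOVA assumes that all observations are independent. When scores from one person are positively correlated, the stable differences between people stay in the error term although they cancel out of every comparison between time points. The F ratio is then too small.

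Two things are at stake, both modest:

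- The plan may report a non-significant ANOVA next to a significant paired test on the same scores, with no rule for choosing between them.
- Hypothesis 2 has no comparator, so a reader could take a within-arm improvement as confirming it. Needling, education, natural course and placebo response are present in both arms and can produce such an improvement without any laser effect.

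**Working it through.** **Inputs from the article.** 53 per group randomised, 42 per group after the allowed 20% dropout, two-sided alpha 0.05, three scores per participant (baseline, 3 days, 8 weeks).

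**Assumed, because the article gives no figure.** Within-person correlation ρ of 0.3, 0.5 or 0.7, equal for all pairs of times; SD of 1 at each time; normal scores. A sustained change means the same shift from baseline at both follow-ups.

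**1. The plan's own figure.** The article states no figure for the within-group tests. Its sample size is for the responder outcome:

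n = (1.96·√(2·0.45·0.55) + 0.842·√(0.30·0.70 + 0.60·0.40))² / 0.30² = (1.379 + 0.565)² / 0.09 = 41.98, so 42 per group. Then 42/0.8 = 52.5, so 53 per group and 106 in total. This reproduces, and nothing below changes it.

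**2. Why the F ratio is too small.** The difference between two time means in the same people has variance 2σ²(1−ρ)/n, but one-way ANOVA uses 2σ²/n. Its standard error is too large by 1/√(1−ρ), which is 1.20, 1.41 and 1.83 at ρ = 0.3, 0.5 and 0.7. With no change over time, the mean square for time has expectation σ²(1−ρ) while the error mean square has expectation σ².

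**3. Type I error, approximation.** With n = 53 and three times, the degrees of freedom are 2 and 53·3 − 3 = 156, and the 5% critical value is 3.054. The true error rate is roughly P(F > 3.054/(1−ρ)). For 2 numerator degrees of freedom, P(F > x) = (1 + 2x/156)^(−78).

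- ρ = 0.3: x = 4.363, P = 1.4%
- ρ = 0.5: x = 6.108, P = 0.28%
- ρ = 0.7: x = 10.18, P = 0.007%

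**4. Simulation, 20,000 runs per setting.** The power columns are for a sustained 0.4 SD change; RM is repeated-measures ANOVA.

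| n | ρ | Type I, one-way | Type I, RM | Power, one-way | Power, RM |
|---|---|---|---|---|---|
| 53 | 0.3 | 1.5% | 5.2% | 52% | 71% |
| 53 | 0.5 | 0.3% | 5.1% | 51% | 85% |
| 53 | 0.7 | 0.01% | 4.8% | 48% | 98% |
| 42 | 0.3 | 1.4% | 5.0% | 41% | 60% |
| 42 | 0.5 | 0.3% | 5.0% | 37% | 75% |
| 42 | 0.7 | 0.03% | 5.4% | 32% | 94% |

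Repeat runs move these figures only in the last digit (for example 1.5% to 1.6% at n = 53, ρ = 0.3). At ρ = 0 the one-way test holds its level (5.0% to 5.1%), so correlation is the cause.

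**5. The alternative reading with change scores only.** If the ANOVA compares just the two changes from baseline, they share each person's baseline and are still correlated. At n = 42 the independent-samples test then has a type I error of about 0.6% to 0.7%, against about 5% for the paired test.

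**6. Conflict with the paired test.** For a 0.4 SD change at n = 53, the paired t-test (baseline against one follow-up) has 82% power at ρ = 0.5 and 96% at ρ = 0.7. The share of trials in which the paired test is significant and the ANOVA is not is therefore at least 82 − 51 = 31% and 96 − 48 = 48%.

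**7. What a within-arm result can show.** Both arms were simulated with an equal 0.5 SD improvement (ρ = 0.5, 42 per arm, 4,000 runs), so the laser adds nothing. The paired test in the active arm was significant in 88% of trials. The baseline-adjusted ANCOVA was significant in 4.6%, close to its nominal 5%.

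**The case against.** The strongest reply has four parts.

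**It may be shorthand.** A condensed article may write one-way ANOVA for one-way repeated-measures ANOVA, and naming the paired tests in the same sentence shows that the authors know the data are paired. This is possible, but the text does not say so. The same section distinguishes independent from paired t-tests, so the missing qualifier cannot simply be supplied. The method is stated, not left to another document.

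**The error is in the safe direction, and the paired tests are sound.** This stands. With positive correlation the ANOVA loses power; it does not create false positives. The paired t-test and the Wilcoxon signed rank test handle the pairing correctly, so the plan keeps a valid within-group test. For large changes the issue disappears: at 1 SD every one of these tests has about 100% power.

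**Hypothesis 2 is already tested properly.** A reader might infer that the within-group tests are the evidence for Hypothesis 2, so that the secondary efficacy claim is invalid. The article does not support that. Nowhere does it assign those tests to the hypothesis. The corresponding aim is about effects of the treatment ("We will investigate the pain reduction, functional limitation improvement, and quality of life improvement effects of 650 nm ILA for NSCLBP"), the secondary outcomes are defined as between-group differences, and a baseline-adjusted ANCOVA is planned for them. Only the missing comparator in the wording remains.

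**A mixed model for the group comparison is a preference.** This also stands. ANCOVA at each of two follow-ups, with the multiple imputation that the article plans, is a valid between-group analysis and need not be replaced.

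**Conclusion.** The point holds as a minor correction. The one-way ANOVA as named does not fit repeated scores from the same participants and is too conservative. At n = 53 its type I error is about 1.5% to 0.01% instead of 5%, and its power for a sustained 0.4 SD change is about 50% against 71% to 98% for a repeated-measures test, over assumed correlations of 0.3 to 0.7. The exact sizes rest on those correlations, on equal correlation between times and on the chosen effect, none of which the article gives. The direction needs only positive within-person correlation.

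The practical consequence is within-group results that can contradict each other without a rule to settle it. The primary responder analysis, the between-group ANCOVA and the 106 participants are unaffected. It would be wrong to conclude that the plan risks a false efficacy claim through this ANOVA, or that its secondary comparisons lack a valid test.

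**What to change.** 1. In Statistical analysis, delete the one-way ANOVA, or replace it with a repeated-measures ANOVA or a mixed model that has a participant term.
2. Label the within-group changes as descriptive, and state that they are not evidence of an effect over sham.
3. Keep the planned baseline-adjusted ANCOVA as the test of the secondary outcomes.
4. Word Hypothesis 2 as greater improvement than control in pain, quality of life and function, so that it matches the definition in Outcome measurements.

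The cost is a few words, best changed before the data are analysed. No new data, visits or participants are needed.
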